### Setting and Sample

3.1

This study will be conducted in one ICU in a national referral hospital in Zambia.

The ICU consists of 10 beds with the ability to provide invasive ventilation, and an additional 10 high‐dependency beds. This ICU provides service to a population of 21 million people, and as a result, the unit admits a wide variety of specialties for both adults and children. While the limitations of a single‐centre study are acknowledged, this facility serves as the primary ICU for the entire country. Therefore, findings will be shared with stakeholders, including the Ministry of Health, the Nursing and Midwifery Council of Zambia (NMCZ), professional organisations such as the Critical Care Nurses Association for Zambia (CCNAZ), ICU leadership teams and hospital management who will participate in all developments for application in practice. They can then lead post‐study projects for transferability to other, smaller ICUs.

#### Participants

3.1.1

Data for Phase 1 will be collected over a 1‐month period in April 2026. Access has been sought and gained (see the Ethics section) to review nursing documentation in patient records. The main ICU consists of 10 beds; accordingly, all patient care plans over a 4‐week period will be audited. A review of admissions and discharge statistics reveals that on average 45 patients a month are admitted. A power calculation for a simple proportion using $n=\frac{Z^{2}P\left(1-P\right)}{d^{2}}$ was carried out to identify the number of patient care plan records to audit [24]. In the calculation, a confidence interval of 95% was used with a 5% degree of error. Z‐score was calculated on the basis of a previous pilot study, which was completed to identify the proportion of records containing evidence of use of the current models. This calculation suggested that 92 records should be audited using a pre‐designed extraction framework. During Phase 1, strategies to recruit participants for the focus groups will be implemented. As a resource‐limited setting there are few critical care nurses with mainly registered nurses working in ICU, and in consequence total population sampling will be used. This includes 10 registered critical care nurses. Therefore, all registered critical care nurses will be invited to participate, with a similar number of registered nurses selected by randomisation from those who volunteer. The ages of potential participants range from 24 to 55, with males comprising approximately one‐third of the total cohort.

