### Data Collection Tools and Methods

3.2

All data will be collected by a Zambian researcher (MK) with support from the international team (CC and JN). A formalised document data extraction grid will be developed, piloted and peer‐reviewed for documentation audit (Table 1) and focus groups (Table 2).

**TABLE 1 nicc70456-tbl-0002:** Documentation audit summary.

Criteria	Rationale
Demographic information and reason for admission.	To identify types of patients admitted and to identify potential nursing problems.
Review of actual written nursing records for terminology, type of nursing care plan and evaluation.	Each section of nursing documentation needs to be considered and compared.
Check whether NANDA‐I checklist is used. Formal NANDA‐I validated list comprising all items of the scale.	To review whether any, some or all criteria are utilised and recorded as part of decision‐making and care provided.
Check Roper, Logan and Tierney's checklist is used. Formal validated list comprising all items of the scale.	To review whether any, some or all criteria are utilised and recorded as part of decision‐making and care provided.
Any other approach/system used identify and create chart for recording.	To review whether any other system of nursing documentation is used as part of decision‐making and care provided.
Standards of nursing documentation.	To identify whether documentation of best practice standards are maintained. To check that documentation is contemporaneous.

**TABLE 2 nicc70456-tbl-0003:** Focus group summary.

Criteria	Rationale
Demographic information.	Information about participants professional career, for example, length of time working in the ICU, type of nurses involved in study and participant numbers.
Semi‐structured interview schedule of eight to nine questions with prompts.	To facilitate discussions and enable key points to be raised—in line with framework analysis guidance.

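### The article takes Z from the pilot, which can only supply P; with Z = 1.96, 92 records give the stated 5% margin only if P is about 6.4% or 93.6%, or more extreme

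*Protocol article*

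**What the plan says.** Section 3.1.1 (Participants) of the protocol article prints the formula for estimating a single proportion, n = Z²P(1-P)/d². It gives the confidence level and margin as follows: "In the calculation, a confidence interval of 95% was used with a 5% degree of error". On the source of the inputs it says: "Z‐score was calculated on the basis of a previous pilot study, which was completed to identify the proportion of records containing evidence of use". The result is: "This calculation suggested that 92 records should be audited using a pre‐designed extraction framework". No value of P appears anywhere in the article.

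The same section says that all care plans over a 4-week period will be audited and that "on average 45 patients a month are admitted".

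Table 1 (section 3.2) has the audit check two models separately, NANDA-I and the Roper, Logan and Tierney activities of daily living. The rationale for each is "To review whether any, some or all criteria are utilised and recorded". The audit will therefore report several proportions.

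**The concern.** In the printed formula each symbol has one source. Z is set by the confidence level, d is the chosen margin, and P is the expected proportion, which is what a pilot measures. The article assigns the pilot to Z and leaves P without a value, so its account of how 92 was reached cannot be right as it stands, and a reader cannot repeat the calculation.

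The margin attached to a fixed number of records also depends strongly on P. A 5% error quoted without P reads as if it applied to the audit in general. Section 4.1 (Development of the Framework) relies on this analysis to show how far the current models are used, and that feeds the new framework. If use of either model, or of some of its criteria, is neither rare nor nearly universal, the estimates will be less precise than the article states.

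**Working it through.** **Inputs.** All come from section 3.1.1: the formula n = Z²P(1-P)/d²; 95% confidence, so Z = 1.96 and Z² = 3.8416; d = 0.05, read as absolute percentage points; n = 92; about 45 admissions a month. P is not stated.

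**Step 1: can 92 be reproduced?** Not directly, because P is missing. Solving for P instead:

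- P(1-P) = n·d²/Z² = 92 × 0.0025 / 3.8416 = 0.0599
- P = [1 ± √(1 - 4 × 0.0599)]/2 = 0.064 or 0.936

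Check: 3.8416 × 0.064 × 0.936 / 0.0025 = 92.05. Exactly 6% or 94% would give 87, so 6.4% and 93.6% are the figures to use. Allowing n from 90 to 94 moves P only between about 6.2% and 6.5%, or 93.5% and 93.8%.

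**Step 2: do small variations rescue a moderate P?** No.

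- Z = 2.0 gives P = 6.1% or 93.9%.
- One-sided Z = 1.645 gives 9.4% or 90.6%.
- If 92 already includes a 10-20% inflation, the low solution is about 5.0% to 5.8%.
- A finite-population correction at P = 50% needs a population of about 121 records, which the article does not give. A population of 45 would give at most 41 records, and one of 540 (12 × 45) would give 225.

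**Step 3: what margin do the records give at other proportions?** Half-width = 1.96 × √[P(1-P)/n]. Example: P = 50%, n = 92 gives 1.96 × √(0.25/92) = 0.102. The last column covers the case where one record means one patient and one average month supplies 45.

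| P | Records needed for ±5 points | Margin with 92 records | Margin with 45 records |
|---|---|---|---|
| 6.4% | 92 (92.05) | ±5.0 | ±7.2 |
| 10% | 139 | ±6.1 | ±8.8 |
| 20% | 246 | ±8.2 | ±11.7 |
| 30% | 323 | ±9.4 | ±13.4 |
| 40% | 369 | ±10.0 | ±14.3 |
| 50% | 385 | ±10.2 | ±14.6 |

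The table is symmetric: 90% behaves like 10%, and so on. Below 6.4% or above 93.6% the margin with 92 records is under 5 points (±4.5 at 5% or 95%).

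**The case against.** The best defence is that 92 may be perfectly correct. A pilot that found about 6.4% of records using the models would give 92 with the stated confidence and margin, and the Background remarks that these models appear to be little applied in practice. The sentence itself says that the pilot was done to find a proportion, so the intended meaning can be guessed, and the pilot's numerical result may stand in a fuller protocol. Sizing a mainly descriptive audit on one headline proportion is also ordinary practice, and other items will naturally have other margins.

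Much of this stands. Nothing in the article contradicts 92, and the missing P alone would be a detail that a condensed article may leave out. What does not go away is that the sentence gives Z a source it cannot have, and that the 5% error is stated without the condition on which it depends.

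A reader might go further and infer that the margin was really 10%, because P = 40% or 60% with d = 10% gives 92.2. The article does not support that. It states neither a 10% margin nor a proportion of 40% or 60%, and a numerical match is not evidence of what was done. It is a reason to confirm d and no more.

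**Conclusion.** The attribution of Z to the pilot is an error in the text. The figure of 92 is unverified, not refuted: it is right if the pilot P was about 6.4% or 93.6%, and only the sponsor can say whether it was. A reader might infer that the sample size is wrong, but without P the article does not show this.

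The stated 5% holds only at that P or at more extreme values. For more moderate proportions, 92 records give margins from about ±6 up to ±10.2 points, roughly double the stated error at worst. These figures assume simple random sampling of independent records, an absolute margin and 92 records in hand. That last assumption is itself open: 92 is about two average months of admissions (92/45 = 2.04), while the audit covers 4 weeks and section 3.1.2 restricts it to invasively ventilated patients. If several records come from one patient, simple binomial margins ignore the clustering.

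This is a correction worth making before the audit starts. It does not invalidate the design.

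**What to change.** In section 3.1.1:

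1. Replace the sentence on the Z-score with wording such as: Z = 1.96 for 95% confidence; P from the pilot = [value].
2. Confirm that this P with the d actually used reproduces 92. If it does not, correct d or n so that the stated inputs and the result agree.
3. Replace the single 5% with the margin expected for each model's proportion, NANDA-I and activities of daily living separately, at the number of records the audit will actually obtain.
4. For that last step, say whether a record is a patient or a care plan, and reconcile 92 with about 45 admissions a month. If only 45 records are available, the margin is about ±7.2 points at 6.4% and ±14.6 at 50%.

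For this point the cost is wording only, and the stated precision becomes less favourable. Whether more records or a longer audit are needed depends on the answer to item 4.

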#### Inclusion and Exclusion Criteria

3.1.2

Inclusion criteria for the retrospective care plan review include invasively ventilated, critically ill patients admitted to ICU, registered nurses and registered critical care nurses working in the main ICU. Exclusion criteria include non‐critically ill patients, for example, post‐operative recovery patients requiring overnight recovery, those admitted to the high‐dependency area and those that do not meet the requirement critical care as outlined by the World Federation of Societies of Intensive and Critical Care Medicine [25] and non‐registered nurses, for example, student nurses, medical staff and other professional groups, such as physiotherapists.

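### The 4-week audit window and the 92-record target in Section 3.1.1 do not fit together: at one record per patient the window gives about 41, and the stated 5% error is not reached

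*Protocol article*

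**What the plan says.** All the figures stand in one paragraph of the protocol article, Section 3.1.1 (Participants).

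- Window: "all patient care plans over a 4‐week period will be audited", with Phase 1 data collection set for one month, April 2026.
- Patient flow: "on average 45 patients a month are admitted", in a main ICU of 10 beds.
- Method: the paragraph opens its sizing with "A power calculation for a simple proportion using" n = Z²P(1−P)/d², and states that "a confidence interval of 95% was used with a 5% degree of error".
- Pilot: the Z-score, rather than P, "was calculated on the basis of a previous pilot study". No value of P is given.
- Target: "This calculation suggested that 92 records should be audited".

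Section 3.1.2 narrows the source further. The care-plan review includes "invasively ventilated, critically ill patients admitted to ICU" and leaves out overnight post-operative recovery and high-dependency patients. The share of admissions that remains is not stated.

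**The concern.** The number of records the window can supply and the number the calculation asks for differ by a factor of about two, and nothing in the article reconciles them. It describes no longer look-back, no rule that a patient contributes several records, and no correction for a finite population.

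The 95% confidence and 5% error are the only quantitative precision target for Phase 1. Its estimate of how far the current nursing models are used is meant to feed the focus groups and, under Section 4.1, the new framework. If the audit ends when the 4 weeks are exhausted, that estimate will be less precise than the article states. If it ends at 92, the window is not 4 weeks, or the records are not independent.

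**Working it through.** **Inputs.** From Section 3.1.1: Z = 1.96 (95%), d = 0.05, target 92, 45 admissions a month, 4 weeks, 10 beds. From Section 3.1.2: ventilated, critically ill patients only, share not given. P is not given.

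**1. The plan's own figure.** Without P, 92 cannot be reproduced directly, so solve for P:

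P(1−P) = 92 × 0.05² / 1.96² = 0.0599, so P = 0.064 or 0.936.

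With the stated d and Z, 92 is right only if the pilot proportion was close to one of these values. For comparison, P = 0.50 would need 385. A d of 0.10 with P = 0.40 also gives 92.2, but 10% is not what the article states. The pilot can supply only P; Z is fixed by the 95% level.

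**2. Yield of the window at one record per patient.**

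- Admissions in 28 days: 45 × 28/30.44 = 41.4, about 41, which is 45% of 92.
- Adding a full unit of 10 patients already in bed: 41 + 10 = 51. On a full month, 45 + 10 = 55.
- Chance does not close the gap: if monthly admissions are Poisson with mean 45 (assumption), the probability of 92 or more is about 6 in 10 billion.

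**3. Precision at that yield.** Half-width = 1.96 × √(0.0599/n), at the P that 92 implies:

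| n | Half-width (points) |
|---|---|
| 92 | 5.0 |
| 55 | 6.5 |
| 45 | 7.2 |
| 41 | 7.5 |

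**4. After the eligibility limits.** The eligible share is an assumption. At 80%, 41.4 × 0.8 = 33 records, half-width 8.4 points. At 40%, 41.4 × 0.4 = 17 records, half-width 11.6 points.

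**5. If a record is one of several plans per patient.** Reaching 92 needs 92/41.4 = 2.2 plans per patient. The design effect is 1 + (2.22 − 1) × ICC, with the intra-patient correlation (ICC) assumed:

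| ICC | Design effect | Effective n | Half-width (points) |
|---|---|---|---|
| 0 | 1.00 | 92 | 5.0 |
| 0.3 | 1.37 | 67 | 5.8 |
| 0.5 | 1.61 | 57 | 6.3 |
| 1 | 2.22 | 41 | 7.5 |

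The 5-point target is met only if plans from one patient are uncorrelated.

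**6. If the window's patients are the whole target population.** A finite-population correction with N = 45 gives 92/(1 + 91/45) = 30. The target would then be about 30, not 92.

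**7. Look-back needed for 92 eligible records.** Months = 92/(45 × share): 2.0 if all admissions qualify, 3.4 at 60% and 5.1 at 40% (shares assumed). Admissions to screen are 92/share: 92, about 153 and 230.

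**The case against.** The strongest reply is that the article never defines a record. It audits care plans, not patients, and Section 3.3 counts how often diagnoses and activities appear. About two plans per patient would bring the count to 92, and a condensed article may leave the definition to a fuller document. This stands to the extent that one cannot say flatly that 4 weeks are unable to produce 92 records; a reader might infer that, but it depends on one record per patient. It does not rescue the calculation, because the simple-proportion formula assumes independent records.

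A second reply is that taking every plan in the window is a census, so sampling error falls away. If so, the target is lower, not 92, and the stated formula has no such correction. Inference to practice beyond those weeks would still need the uncorrected number.

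A third is that Phase 1 is descriptive, has no confirmatory hypothesis, and belongs to a study that Section 5 already calls small. That is fair, and it limits the consequences: with P near 0.064 or 0.936, ±7.5 points still describes the models as rarely or nearly always used. It does not make the stated 5% correct.

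Two stronger readings are tempting but not supported:

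- A reader might set the half-width at P = 50% (15.3 points at n = 41) against the stated 5. That mixes the shortfall with a different P: at P = 50% even the full 92 records would give only ±10.2.
- A reader might infer that nurses would alter their documentation because "During Phase 1, strategies to recruit participants for the focus groups will be implemented". The article calls the review retrospective and does not say that the audited plans are written in April 2026, so this is speculation.

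**Conclusion.** The point holds as an internal inconsistency. On one record per patient, the 4-week window supplies about 41 records, at most about 51 to 55 with patients already in bed, against 92 required. At the proportion that 92 implies, the half-width is about ±7.5 points (±6.5 at n = 55) instead of ±5.

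It is wider again once non-ventilated and other excluded patients are removed, but by how much is unknown: the 17 to 33 records shown for 40% to 80% eligibility rest on an assumed share. Reading a record as one of about 2.2 plans per patient reaches the count and still misses the precision, unless plans within a patient are uncorrelated. A census reading changes the target itself. So 92 and 4 weeks do not fit on any reading the text supports.

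The back-solved P assumes that the stated 5% and 95% are what was actually used. Because P is not reported, the 92 cannot be verified. The shortfall against 92 does not depend on P.

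**What to change.** In Section 3.1.1:

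1. State the pilot proportion P, attribute it (not Z) to the pilot, and confirm that it gives 92 with d = 0.05; if it does not, correct the target.
2. Define the record as one care plan per eligible patient, with a fixed rule for which plan is taken when a patient has several.
3. Then choose one of two routes:
   - Replace the 4-week window with a consecutive retrospective look-back that stops when 92 eligible records are reached (or the corrected target from item 1). April 2026 can remain the extraction month.
   - Keep the 4 weeks, delete the 92 records and the 5% error, and state the half-width that the expected number of eligible records gives.

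The first route uses existing files and extracts no more records than the 92 already planned. Its costs are an older window (about 2.0 to 5.1 months, depending on the eligible share) and more screening, about 230 admissions if only 40% qualify. The team should also check that the access already granted covers the longer look-back. The second route costs only wording and an openly stated loss of precision.

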#### Inclusion and Exclusion Criteria

3.1.2

Inclusion criteria for the retrospective care plan review include invasively ventilated, critically ill patients admitted to ICU, registered nurses and registered critical care nurses working in the main ICU. Exclusion criteria include non‐critically ill patients, for example, post‐operative recovery patients requiring overnight recovery, those admitted to the high‐dependency area and those that do not meet the requirement critical care as outlined by the World Federation of Societies of Intensive and Critical Care Medicine [25] and non‐registered nurses, for example, student nurses, medical staff and other professional groups, such as physiotherapists.

### Data Collection Tools and Methods

3.2

All data will be collected by a Zambian researcher (MK) with support from the international team (CC and JN). A formalised document data extraction grid will be developed, piloted and peer‐reviewed for documentation audit (Table 1) and focus groups (Table 2).

**TABLE 1 nicc70456-tbl-0002:** Documentation audit summary.

Criteria	Rationale
Demographic information and reason for admission.	To identify types of patients admitted and to identify potential nursing problems.
Review of actual written nursing records for terminology, type of nursing care plan and evaluation.	Each section of nursing documentation needs to be considered and compared.
Check whether NANDA‐I checklist is used. Formal NANDA‐I validated list comprising all items of the scale.	To review whether any, some or all criteria are utilised and recorded as part of decision‐making and care provided.
Check Roper, Logan and Tierney's checklist is used. Formal validated list comprising all items of the scale.	To review whether any, some or all criteria are utilised and recorded as part of decision‐making and care provided.
Any other approach/system used identify and create chart for recording.	To review whether any other system of nursing documentation is used as part of decision‐making and care provided.
Standards of nursing documentation.	To identify whether documentation of best practice standards are maintained. To check that documentation is contemporaneous.

**TABLE 2 nicc70456-tbl-0003:** Focus group summary.

Criteria	Rationale
Demographic information.	Information about participants professional career, for example, length of time working in the ICU, type of nurses involved in study and participant numbers.
Semi‐structured interview schedule of eight to nine questions with prompts.	To facilitate discussions and enable key points to be raised—in line with framework analysis guidance.

### Data Analysis

3.3

The retrospective review of nursing care plans will use the extraction framework as indicated in Table 1. Data will be collected and transferred into a MS Excel spreadsheet. Data will be numerical: for example, how many times a NANDA‐I diagnosis is used and how many times the ADLs are included. This approach was seen as a practical measure to assess actual usage of the current recommended models. Descriptive statistics will be used to determine patterns and trends [26]. Where possible, tests for significant difference such as chi‐squared will be used to determine significant differences, as the majority of the data will be nominal or ordinal [27]. For open‐ended questions, data will be coded and analysed using framework analysis processes [23].

Focus groups will be conducted with different nursing groups as outlined above. A maximum of six participants will be invited to each focus group, and MS Teams will be used to record the discussions, as this will facilitate immediate transcribing. Focus groups will be scheduled during the handover period to allow participants to attend, to reduce the impact on patient care and will be conducted in an office away from the clinical area, but within the hospital. Following the focus group, the MS Teams transcript will be downloaded and saved as an MS Word document. Framework analysis will then be used to analyse the interviews [23]. Only the research team will have access to the raw data sets. All data will be analysed by the research team, including a Zambian Researcher who will provide context validation for the coding process. Framework analysis is considered more transparent and robust than thematic analysis [28]. Open coding of the transcript entails constant comparisons supporting the emergence of initial categories. A more focussed second in‐depth analysis includes reviewing data for context [28, 29]. This iterative analysis facilitates interconnectedness [28, 30], facilitating analysis, both within and across data sets [29]. This will include searching for phrases that fit with the Ubuntu philosophical discussion.

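### The 5% margin comes from a random-sample formula, but the audit takes every care plan from one 4-week block, so the margin does not apply to the usual practice it is meant to describe

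*Protocol article*

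**What the plan says.** Section 3.1.1 (Participants) of the protocol article fixes both the window and the sample size.

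- **Window:** "Data for Phase 1 will be collected over a 1‐month period in April 2026", and "all patient care plans over a 4‐week period will be audited".
- **Method:** the number of records comes from "A power calculation for a simple proportion using" n = Z²P(1−P)/d².
- **Precision:** "a confidence interval of 95% was used with a 5% degree of error".
- **Result:** "This calculation suggested that 92 records should be audited".
- **Expected proportion P:** not given. The pilot is attached to Z instead ("score was calculated on the basis of a previous pilot study").
- **Throughput:** the same section reports an average of 45 admissions a month. Section 3.1.2 then restricts the review to invasively ventilated, critically ill patients.

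For the analysis, section 3.3 states "Descriptive statistics will be used to determine patterns and trends", and the Abstract (Methods) has similar wording. The Abstract and section 3.3 present Phase 1 as showing how far the current models are actually used. Section 5 (Limitations) concedes small scale and a single centre but holds that the findings may generalise. It does not mention that the records come from a single period.

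**The concern.** The formula gives the precision of a simple random sample drawn from the population being described. Here the population of interest is nursing documentation on this unit as it is currently practised, and the records are every care plan from one unbroken four-week stretch. If use of the models differs from month to month, all records share whatever was particular to that stretch. Adding more records from the same stretch cannot average this out, and the stated 5% does not include it.

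Phase 1 is the quantitative base for the focus groups and, with them, for the new framework. If its proportion is reported with a ±5-point interval, readers will take usual practice to be known more precisely than this design allows.

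**Working it through.** **Inputs.** From section 3.1.1: 95% confidence (Z = 1.96), d = 0.05, n = 92, 45 admissions a month, a 4-week window. Not in the documents: P, the between-month SD (s), and the share of admissions that are eligible.

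**1. The plan's own figure.** Without P, 92 can only be solved backwards. With P = 0.064:

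n = 1.96² × 0.064 × 0.936 / 0.05² = 92.0

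P = 0.936 gives the same n. So 92 is consistent with the formula at P of about 6.4% (or 93.6%), but it cannot be confirmed. P = 0.064 is used below.

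**2. What the margin refers to.**
- *The four weeks themselves:* all plans are audited, so the proportion for that period is known without sampling error and no ± applies.
- *Usual practice on the unit:* a margin has meaning here, but the block is not a random sample of it. The formula has no term for variation between periods.

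**3. Allowing for month-to-month variation.** For one block of 92 records, the half-width for usual practice is 1.96 × √(s² + P(1−P)/92). For 92 records spread over 12 months it is 1.96 × √(s²/12 + P(1−P)/92). Here P(1−P)/92 = 0.0599/92 = 0.000651.

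| Assumed s (points) | One block | 12 months |
|---|---|---|
| 0 | ±5.0 | ±5.0 |
| 1 | ±5.4 | ±5.0 |
| 2 | ±6.4 | ±5.1 |
| 3 | ±7.7 | ±5.3 |
| 5 | ±11.0 | ±5.7 |

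For example, at s = 5 one block gives 1.96 × √(0.0025 + 0.000651) = 0.110, and 12 months gives 1.96 × √(0.000208 + 0.000651) = 0.057. The 12-month column treats the months as a sample of longer-run practice. If the target is that year only, a simple random sample of it needs no between-month term.

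**4. Records available in the block.** In 28 days of a 30-day month, 45 × 28/30 = 42 admissions, so the block yields about 42 to 45 records if one record is one patient, before the ventilated-only restriction. Reaching 92 would take 92/45 = 2.04 months. Even with no between-month variation, the half-widths are:
- n = 45: 1.96 × √(0.0599/45) = 0.072
- n = 42: 1.96 × √(0.0599/42) = 0.074

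The block therefore gives at least ±7.2 points at the implied P.

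**5. Whether 12 months would supply 92 eligible records.** 12 × 45 = 540 admissions, and 92/540 = 17%. A year is long enough if at least about 17% of admissions meet the eligibility criteria. The documents do not give that share.

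**The case against.** A consecutive audit of all records is an ordinary and practical way to describe current use, and it avoids any choice of records. No decision in the article turns on a 5-point margin; Phase 1 informs focus groups and stakeholder work. No document gives a between-month SD. At 1 point, spreading the records changes the half-width only from ±5.4 to ±5.0. At 5 points against a mean of 6.4%, a normal model would put about 10% of months below zero use, so the upper end of the range is strained. All of this stands, and it is why the size is given as a range and the point is not treated as invalidating the study.

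Some stronger readings are tempting, but the documents do not support them.

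- *The 5% margin is valid for that month.* It is not: a complete audit of the month has no sampling margin for the month. Labelling the interval as describing that month would add a new error.
- *The plan promises a trend over calendar time that one block cannot show.* Section 3.3 describes counts of how often each model is used, and *trends* may simply mean tendencies in recording. Four weeks is a period, not a single time point, and week-by-week description is possible, although none is planned.
- *All records share one rotating group of staff.* The article does not describe staff rotation.
- *The block contains 92 records.* On one record per patient it does not. If patients contribute several records, 92 may be reachable, but those records are clustered within patients, which the formula also ignores.

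Because the review is retrospective, April 2026 may be the month of extraction and not the month the records date from. The frame is one 4-week block either way.

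**Conclusion.** The concern holds in a limited form. The formula and the design in section 3.1.1 do not fit each other: a ±5-point margin that assumes simple random sampling is attached to a complete audit of one block, while the Abstract and sections 3.3 and 5 use the result for practice beyond that block. The mismatch follows from the text alone.

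Its size rests on assumptions. At n = 92 and P = 6.4%, a between-month SD of 1 to 5 points turns ±5.0 into about ±5.4 to ±11.0. Separately, one record per patient limits the block to about 42 to 45 records and at least ±7.2 points, before ineligible patients are removed. The study remains usable, but its stated precision is not a property of this design. The change is worth making because it is cheap.

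**What to change.** **Preferred.** Keep extraction in April 2026. Draw the stated 92 eligible records at random from the ICU admissions register over a longer preceding period, for example 12 months (92/12, about 8 per month), and tabulate use by month. The simple-proportion formula then matches the sampling, and 92 becomes reachable subject to the 17% eligibility check above. The review is retrospective and section 3.1.1 says record access has been obtained, so this means rewriting the sampling paragraph, confirming that the access covers the longer period, and retrieving older records. No records are added to the planned 92. The downside is that some archived records may be missing; these should be counted and reported.

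**If the 4-week block is kept.** Remove the 5% margin and the target of 92 from section 3.1.1, and report the result as a complete audit of that period. Add the single period to the limitations in section 5, and reduce *patterns and trends* to *patterns* in the Abstract and section 3.3. This costs only wording, but it gives up any stated precision for usual practice.
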